# High-dose single-fraction IMRT versus fractionated external beam radiotherapy for patients with spinal bone metastases: study protocol for a randomized controlled trial

**DOI:** 10.1186/s13063-015-0761-7

**Published:** 2015-06-09

**Keywords:** Bone metastases, Spine, SBRT, IMRT, Palliative radiotherapy

## Abstract

**Background:**

Stereotactic body radiation therapy (SBRT)using intensity-modulated radiotherapy (IMRT) can be a safe modality for treating spinal bone metastasis with enhanced targeting accuracy and an effective method for achieving good tumor control and a rigorous pain response.

**Methods/design:**

This is a single-center, prospective randomized controlled trial to evaluate pain relief after RT and consists of two treatment groups with 30 patients in each group. One group will receive single-fraction intensity-modulated RT with 1×24 Gy, and the other will receive fractionated RT with 10×3 Gy. The target parameters will be measured at baseline and at 3 and 6 months after RT.

**Discussion:**

The aim of this study is to evaluate pain relief after RT in patients with spinal bone metastases by means of two different techniques: stereotactic body radiation therapy and fractionated RT. The primary endpoint is pain relief at the 3-month time-point after RT. Secondly, quality of life, fatigue, overall and bone survival, and local control will be assessed.

**Trial registration:**

ClinicalTrials.gov identifier NCT02358720 (June 2, 2015).

## Background

The vertebral column is the main localization of bone metastases and is where they frequently indicate an advanced stage of a malignant primary disease [1, 2]. Two thirds of all patients with tumors are estimated to develop bone metastases in the course of their disease [3]. Spinal bone metastases are of central impact for patients in a palliative setting. The clinical symptoms include pain at rest and under exercise but also impaired activity of daily life, the risk of pathological fractures, and neurological deficits. Pain is the essential factor for decreased quality of life (QoL) of patients with bone metastases. In regard to pain therapy and re-calcification of former osteolytic lesions, palliative radiotherapy (RT) represents an effective treatment option [4]. The most common schedule was specified as 30 Gy in 10 fractions. The outcome showed a partial pain response in 50 % to 80 % of patients and a complete pain response in one third [5]. Stereotactic body radiation therapy (SBRT) using intensity-modulated radiotherapy (IMRT) can be a safe modality for treating spinal metastasis with enhanced targeting accuracy [6]. Secondly, IMRT to the spine was well tolerated (especially in the spinal cord), had no significant late toxicities, and spared other organs at risk simultaneously [7]. Pretreatment megavoltage computed tomography (CT) allows clinicians to position control and correction to determine the localization of the metastasis, and to hold a divergence of the dose of the local region most minimally [8]. Nguyen *et al*. [9] showed that SBRT with 24 Gy is a safe and effective treatment modality that can be used to achieve good tumor control and palliation of pain associated with spinal metastases. To the best of our knowledge, no comparable randomized study has been described in the literature so far.

The aims of this study were to apply a high biological dose in the tumor region and to achieve a comparable result related to pain relief and local control on the one hand and to reduce the overall treatment time for palliative patients with painful spinal bone metastases on the other hand. Secondly, the aim was to evaluate QoL, fatigue, and survival.

## Methods/design

This is a single-center, prospective randomized controlled trial with parallel-group design to determine the pain relief after RT in patients with spinal bone metastases. Two different techniques were evaluated: high-dose single-fraction IMRT with 1×24 Gy and fractionated external beam RT with 10×3 Gy. Prior to enrolment in the study, the patients will undergo a staging of the vertebral column in connection with their CT for RT planning and magnetic resonance imaging (MRI) to measure the spinal cord dimension. After the baseline results have been recorded, the patients will be randomly assigned to one of the two groups: single-fraction IMRT 1×24 Gy (n = 30) or fractionated RT 10×3 Gy (n = 30). The target parameters will be measured and recorded at baseline, at the end of RT (t_1_), and at 12 weeks (t_2_) and 6 months (t_3_) after the end of the irradiation period (Fig. 1).

**Fig. 1 Fig1:**
[figure not shown]
Flowchart of the study. CT, computed tomography; IMRT, intensity-modulated radiotherapy; MRI, magnetic resonance imaging; RT, radiotherapy

### Recruitment and randomization

The patients will be given information on the study by the medical personnel of the RT department in connection with the planning of the RT schedule (about 1 to 2 weeks prior to the start of RT). If they are interested in participating in the study, the study candidates will be given the patient information sheet, including the declaration of informed consent, with the request that they re-read the information carefully and, if they consent to the conditions, return the signed declaration at the next appointment. Patients will be given the opportunity to ask the study staff further questions. Informed consent will be obtained from each participant prior to enrolment in the study. Among the preconditions for participation in the study is the condition that no metastatic spinal cord compression (tumor distance of more than 3 mm to spinal cord) of the metastasized vertebral body be detected in the MRI recorded during the planning procedure.

A block randomization procedure shall be used to ensure the even distribution of patients into two intervention groups, stratified at baseline by pain level. The patients shall then be assigned 1:1 to one of the two treatment groups on the basis of the baseline measurements. The randomization procedure shall be carried out by a central office. The study personnel responsible for the recruitment and baseline measurements shall have no access to the randomization list. The recruitment phase shall be concluded with the attainment of the planned number of patients (60 patients in total). It shall last 12 months and was scheduled to start in December 2014. Regular study participation shall end 6 months after enrolment in the study or, where applicable, with the respective patient’s death.

### Inclusion criteria

Patients with a histologically confirmed tumor diagnosis and with secondary diagnosed solitary/multiple spinal bone metastasesIndication for RT of the spinal bone metastasesMaximum of two irradiated vertebral bodies per regionMaximum of two different vertebral regionsAge of between 18 and 80 yearsKarnofsky index [10] of at least 70Signed declaration of informed consentTumor distance of more than 3 mm to spinal cord.Exclusion criteriaMultiple myeloma or lymphomaSignificant neurological or psychiatric disorders, including dementia and epileptic seizuresContraindication for MRIPrevious RT at the current irradiation siteOther severe disorders that in the judgment of the study director may prevent the patient’s participation in the studyLacking or diminished legal capacityAny medical of psychological condition that the study director considers a preventive factor for the patient’s ability to complete the study or to adequately understand the scope of the study and to give his or her consent.

### Assessment of the primary and secondary endpoints

The aim of the trial is to evaluate pain relief after RT in patients with spinal bone metastases. Two different techniques are evaluated: single-fraction IMRT with 1×24 Gy and fractionated external beam RT with 10×3 Gy. The primary endpoint is defined as pain relief of more than 2 points according to visual analog scale (VAS) measured at the irradiated region at the 3-month time-point after the end of RT (t_2_). Secondary endpoints are QoL, fatigue, pain, overall survival, bone survival, local control, pathological fracture, and neurological deficit. The baseline examination shall be carried out on the first day of RT prior to the start of therapy and is scheduled to comprise the comprehensive recording of the socio-demographic data, the recording of the current pain situation, the fear of suffering fractures, the QoL, and the current degree of fatigue. The follow-up examinations shall take place after the end of RT (day of the last fraction) and 12 weeks and 6 months after RT, measuring those parameters recorded at the baseline examination. The further follow-up examinations shall correspond to those carried out as standard after-care investigations.

The secondary endpoints such as fatigue, QoL, and anxiety shall be recorded by using validated questionnaires (EORTC QLQ FA13 [11], EORTC QLQ BM22 [12], and the questionnaire to record stress in patients with cancer (FBK) according to Book *et al*. [13]). All patients will also be asked to record their pain history by using a pain diary (documentation of medication daily during treatment, once weekly after the end of treatment, VAS pain scale). Furthermore, the local control is assessed by means of CT images taken prior to and 3 and 6 months after RT. The pain response is documented on the VAS (range of 0 to 10). Complete response is defined as VAS score of 0 after 3 and 6 months, and partial response is defined as a score improvement by at least 2 points after 3 and 6 months, according to the international consensus response categories of Chow *et al*. [14]. Overall survival is defined as time from initial diagnosis until death, and bone survival is defined as time from initial diagnosis of spinal bone metastasis until death.

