### Radiotherapy

Treatment is simulated with a CT simulator by using a 3-mm slice thickness taken within the involved vertebral region. Immobilization is ensured with an Aquaplast head mask (Aquaplast Corporation, Wyckoff, NJ, USA), vacuum mattress, and Wingstep® (Elekta, Stockholm, Sweden). On the basis of the planning CT, risk organs and clinical target volume (CTV) are contoured. The spinal cord is contoured on the basis of visible target on the CT scan with the help of fusion with MRI. CTV confirmed planning target volume (PTV). The dose of PTV occurred at the 80 % isodose, encircling the PTV. The RT procedure in group A is conducted as IMRT (tomotherapy or step-and-shoot IMRT or volumetric modulated arc therapy) 24 Gy in a single fraction at the 80 % isodose. In group B, RT is performed as irradiation of the involved vertebral body as well as the ones immediately above and below to a total dose of 30 Gy with a single daily dose of 3 Gy using 6 MV individually formed beams (Linac, multileaf collimator) after CT scan-based 3D planning. The same tolerance doses of the organs at risk as in the RTOG 0631 study are used [15].

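### Baseline is needed before randomisation but is taken on the first RT day, when the arm is probably known; and t1 falls 0 days after baseline in group A but about 9 to 13 days after in group B

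*Protocol article*

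**What the plan says.** All references are to the protocol article.

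- **Order of baseline and allocation.** Methods/design: "After the baseline results have been recorded, the patients will be randomly assigned to one of the two groups". Recruitment and randomization: the block randomisation is "stratified at baseline by pain level", and "The patients shall then be assigned 1:1 to one of the two treatment groups on the basis of the baseline measurements".
- **Date of baseline.** Assessment of the primary and secondary endpoints: "The baseline examination shall be carried out on the first day of RT prior to the start of therapy". This examination includes current pain, quality of life and fatigue.
- **Planning.** Recruitment and randomization says patients are informed "in connection with the planning of the RT schedule (about 1 to 2 weeks prior to the start of RT").
- **Treatment by arm.** Radiotherapy: group A receives IMRT, "24 Gy in a single fraction at the 80 % isodose". Group B receives 30 Gy at 3 Gy per day, 3D-planned, to the involved vertebra and its two neighbours.
- **Follow-up dates.** Assessment of the primary and secondary endpoints: "The follow-up examinations shall take place after the end of RT (day of the last fraction"), with further visits 12 weeks (t2) and 6 months (t3) after RT.
- **Concealment.** Recruitment and randomization: "The study personnel responsible for the recruitment and baseline measurements shall have no access to the randomization list". No masking of patients or assessors is described.

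**The concern.** The primary endpoint is a responder classification built on the fall in self-reported VAS from baseline to t2. Its reference value should be fixed before anyone knows the arm. If the reference is taken on the first RT day and the arm is already known, a patient's expectations about one fraction or ten can enter the baseline score and hence the change score. Withholding the randomisation list from staff does not prevent this, because it protects allocations still to come, not one already made.

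There is also a question of which score is used. If allocation precedes the first RT day, the pain level used for stratification cannot be the baseline described in the endpoint section, and no other measurement is named.

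The t1 visit raises a different problem. It is tied to the end of a course that lasts one day in one arm and ten fractions in the other. Pain, quality of life and fatigue would be compared after unequal intervals.

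**Working it through.** The plan gives no figure on this point. Its one calculated figure, a detectable standardised effect of 0.74 with 30 per group, reproduces (two-sided t-test, 80 % power: 0.736) and is not affected.

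**Baseline: the sections side by side**

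1. Methods/design and Recruitment and randomization fix the order: baseline pain, then allocation.
2. The endpoint section fixes the date of baseline: first RT day, before treatment.
3. Together these put allocation on the first RT day, between the baseline examination and the first fraction.
4. The Radiotherapy section makes technique, target volume and fractionation specific to the arm, so the first fraction needs a plan for that arm. The planning CT and MRI precede enrolment and can serve both arms; the plan itself cannot.
5. The article describes neither randomisation on the first RT day nor preparing both plans for every patient. It places planning of the RT schedule about 1 to 2 weeks before RT.
6. So either an undescribed same-day procedure is used, or allocation comes before the endpoint section's baseline and the order in step 1 is not kept.

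**What a shifted baseline could do**

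Let D = baseline VAS − VAS at t2, with response when D reaches the cut-off c. If baseline is reported s points higher, D becomes D + s. Only patients with c − s ≤ D < c change status; those already at or above c do not. A downward shift affects only the other side. The documents give no basis for the size or direction of s, or for a difference between arms. As a scale: one reclassified patient is 1/30 = 3.3 percentage points of an arm's responder rate.

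**t1: days from baseline**

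Inputs: baseline on the day of fraction 1; t1 on the day of the last fraction; one fraction in A; 30/3 = 10 daily fractions in B. The article does not say whether weekends are treated, so both cases are shown.

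| Arm and schedule | Calculation | Baseline to t1 |
|---|---|---|
| A, one fraction | first day = last day | 0 days |
| B, every calendar day | 10 − 1 | 9 days |
| B, weekdays, Monday start | 9 + one weekend (2) | 11 days |
| B, weekdays, Tuesday to Friday start | 9 + two weekends (4) | 13 days |

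**t2: days from baseline**

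12 weeks = 84 days after the end of RT. A: 0 + 84 = 84. B: 84 + 9 to 84 + 13 = 93 to 97. Both arms are equal when counted from the end of RT.

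**The case against.** **The sections do not contradict each other word for word.** No sentence says that allocation precedes the first RT day; baseline, central randomisation and first fraction could all fall on that day. The 1 to 2 weeks dates the giving of information, not the allocation, and a condensed article may leave out logistics. This stands as far as it goes. A reader might infer an outright contradiction, or that baseline certainly follows an unmasked allocation, and the text supports neither. But same-day allocation is hardly workable with arm-specific plans, and if it is intended the article should say so.

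**t1 carries little weight.** The primary endpoint is at t2, response is defined at 3 and 6 months, the abstract lists no end-of-RT visit, no between-arm test at t1 is specified, and all tests are called descriptive. All of this is correct and limits the consequence. It does not make t1 comparable: pain, quality of life and fatigue are scheduled there in both arms.

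**The direction is unknown.** A reader might infer that t1 favours group B because it has had longer to respond. The documents do not support that: fatigue or quality of life could be worse at the end of ten fractions, which would favour group A.

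**t2 and t3 need not be moved.** This stands. Both are timed identically from the end of RT, the offset from baseline at t2 is 9 to 13 days on 84, and counting from the first fraction would only shift the inequality to time since completion.

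**The diary may not fill the gap.** It is tempting to read it as giving a weekly VAS after treatment. The weekly frequency is attached to medication, and the VAS frequency is ambiguous. It is not described as recording quality of life or fatigue.

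**Conclusion.** Two separate points hold.

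1. The timing of baseline and the order of randomisation are not workable together as written. The reference VAS for the primary endpoint could be recorded with the arm known. This rests on the assumption that an arm-specific plan is made before the first RT day and that both plans are not routinely prepared. No size can be given for any resulting bias.

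2. At t1, group A is measured on its baseline day and group B 9 to 13 days later (11 to 13 with weekday treatment). This follows directly from the stated schedule. A between-arm comparison at t1 is confounded with elapsed time in an unknown direction.

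The timing of t2 and t3 and the sample-size statement are not in question. The change should be made because the first point touches the primary endpoint and the cost is low.

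**What to change.** **Baseline.** Record the VAS and questionnaires after consent and before randomisation. Use that one measurement as stratifier and as reference for the change score, and align Methods/design, Recruitment and randomization, and the endpoint section accordingly. A VAS on the first RT day can be kept as an additional reading, which also shows any drift during planning. If same-day randomisation is in fact intended, state that instead, including how arm-specific plans are ready. As the trial is already recruiting, report for patients enrolled so far which pain score was used and whether it preceded allocation.

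**t1.** Either time the early assessment from a common origin in both arms, for example about 2 weeks after the first fraction, or keep t1 on the last-fraction day, report it within arm only and make no between-arm test. With the first option, the visit falls 14 − 13 = 1 to 14 − 9 = 5 days after group B's last fraction, close to its present t1.

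**t2 and t3.** Leave them anchored to the end of RT.

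**Cost.** Reconciled wording in three sections, an earlier date for measurements already planned, and at most one mailed questionnaire, including the VAS, in group A. No treatment changes.

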### Statistical analysis

The total number of patients undergoing RT in the Department of Radiation Oncology at the University Hospital Heidelberg for metastatic processes in the vertebral column in the recruitment period is about 120, and about 90 of them shall fulfill the inclusion criteria within 1 year. On account of the explorative character of this study, it is not possible to estimate the total number of cases; however, with a scheduled number of 30 patients per group, it will be possible to detect a standardized mean value effect of 0.74 with a power of 80 % and a significance level of 5 % when a normal distributed variable is examined. The primary endpoint is a categorical variable (the percentage of patients achieving at least a 2-point decrease in pain according to the VAS). Means, standard deviations, medians, and minimum and maximum or absolute and relative frequencies will be reported according to the scale level of the variables. The results will be reported as *P* values. For all analyses, a *P* value of 0.05 or less will be considered significant, and results of appropriate statistical tests will be of a descriptive nature and have no confirmatory value. Wherever possible, statistical graphics will illustrate the findings.

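### Complete response needs only a VAS of 0, with no fall from baseline and no entry pain level, so some complete responders fail the primary endpoint

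*Protocol article*

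**What the plan says.** All of this is in the protocol article.

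- **Complete response** (Assessment of the primary and secondary endpoints): "Complete response is defined as VAS score of 0 after 3 and 6 months". This is a level, with no condition on baseline or change.
- **Partial response** (same sentence): "partial response is defined as a score improvement by at least 2 points after 3 and 6 months". This is a change, with no condition on the level reached. The sentence closes by placing both categories "according to the international consensus response categories".
- **Primary endpoint**, at 3 months. The endpoint section says "The primary endpoint is defined as pain relief of more than 2 points according to visual analog scale (VAS"), whereas Statistical analysis says "the percentage of patients achieving at least a 2-point decrease in pain according to the VAS".
- **Entry**: the inclusion and exclusion criteria ask for an indication for radiotherapy. None of them mentions pain or a minimum VAS.
- **Baseline pain elsewhere**: randomisation is "stratified at baseline by pain level", without stated cut-offs. The aims in the Background refer to "palliative patients with painful spinal bone metastases".

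**The concern.** The primary endpoint and partial response measure change, while complete response measures a level that a patient may already have at entry. Two things follow.

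First, a patient with no pain to relieve can be counted in the best response category. The same patient is then a complete responder in one table and a non-responder in the primary table.

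Second, the categories are not exclusive. A patient going from 5 to 0 satisfies both definitions, because partial response does not exclude VAS 0.

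At stake is how the pain results read together. The CR rate would include some patients without the fall in pain that the trial calls relief. CR and PR counts could not be set against the primary responder percentage without explanation.

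**Working it through.** The only computed figure in Statistical analysis is the detectable standardised effect of 0.74 with 30 per group. It reproduces (two-sided t-test, 5% level, 80% power: 0.736), and this point does not depend on it. The protocol gives no figure for CR, so the check is to apply the stated rules.

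**Step 1: apply the rules to a follow-up VAS of 0.** Fall = baseline − 0.

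| Baseline | Fall | CR | Primary, more than 2 | Primary, at least 2 |
|---|---|---|---|---|
| 0 | 0 | yes | no | no |
| 1 | 1 | yes | no | no |
| 2 | 2 | yes | no | yes |
| 3 to 10 | 3 to 10 | yes | yes | yes |

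CR is not contained in the primary responders under either wording. Baselines 0 and 1 break it under both, and baseline 2 only under the stricter one.

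**Step 2: overlap.** Baseline 5, follow-up 0: the level is 0, so CR; the fall is 5, which is at least 2, so PR as well. The same holds for any baseline of 2 or more.

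**Step 3: size, under assumptions.** The baseline distribution is not given. Without treatment effect or measurement noise, the CR rate simply equals the share entering at VAS 0. With 30 per arm, one such patient moves an arm's CR rate by 1/30 = 3.3 points.

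To add noise, 400,000 patients per scenario were simulated with no treatment effect. Baseline is an integer with assumed shares at VAS 0, 1 and 2 and the rest uniform over 3 to 9. Within-patient SD is 1.0 or 1.5. Follow-up is baseline plus the difference of two measurement errors (variance 2 × SD²), rounded and clipped to 0–10. The two-visit column requires VAS 0 at both 3 and 6 months, with the baseline error shared by both differences.

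| Assumed shares at VAS 0/1/2 | CR rate, one visit | of which fall below 2, one visit | CR with fall below 2, both visits |
|---|---|---|---|
| 5/5/5% | 6–9% | about 5 points | about 3.4 points |
| 10/5/5% | 9–11% | about 8 points | about 5.5–5.9 points |
| 15/10/5% | 14–16% | about 13 points | about 9 points |

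- With fully independent errors at the two visits, the last column falls to about 2.6, 4.5 and 7 points.
- Under the stricter primary wording, the one-visit figures rise to about 6, 9 and 14 points.
- Requiring a fall of at least 2 points as well leaves a one-visit CR rate of 1–4% in every scenario.
- In the 5/5/5% scenario about 2 of the 5 points are patients going from 1 to 0, not patients who were pain-free throughout.

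**The case against.** The strongest reply is that the sentence refers to a published consensus, which may carry its own baseline condition, and that the evaluable set is often left to the full protocol or SAP. Neither can be checked here. What stands against the reply is that the article restates the rule in its own words without such a condition. If the source has one, writing it in is the correction sought.

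The second reply is that patients will have pain, since the aims speak of painful metastases. That makes entrants at VAS 0 less likely but is not an entry criterion. The Discussion also names prevention of fractures and neurological deficits among the therapy goals, so an indication for radiotherapy need not imply pain. Still, no document supports any particular share at VAS 0 to 2.

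A reader might also draw stronger conclusions that the text does not support:

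- **That the primary result is inflated.** CR falls under pain among the secondary endpoints, the primary endpoint requires a fall, and the tests are declared to have no confirmatory value.
- **That chance numbers of pain-free entrants will unbalance the arms.** Randomisation is stratified by pain level, which limits this. Some imbalance within a stratum is possible because the cut-offs are not stated.
- **That every pain-free entrant becomes a complete responder.** This happens only if VAS is still 0 at follow-up.
- **That all these patients had no relief.** A patient going from 1 to 0 lost all recorded pain, but by less than the primary cut-off.
- **That CR plus PR must equal the primary count.** The protocol nowhere says so, and part of the mismatch comes from its two primary cut-offs.

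**Conclusion.** The point holds as a defect in a stated secondary definition. As written, 0 to 0 and 1 to 0 are complete responses and primary failures under both primary wordings; 2 to 0 is so under the stricter one. CR and PR also overlap. These statements need no assumption beyond the text.

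The size does need assumptions. It is nil if nobody enters at VAS 0 to 2. With 5 to 15% assumed at VAS 0, the share of patients who are CR without a 2-point fall is roughly 3 to 9 percentage points if VAS 0 is required at both visits, and 5 to 13 points at a single visit. The phrase about 3 and 6 months can be read either way. The consequence is for the reading of the secondary pain tables, not for the primary comparison. The correction is worth making because it is cheap.

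**What to change.** 1. Reconcile the primary cut-off between the endpoint section and Statistical analysis, since the response definitions depend on it.
2. Define CR as VAS 0 at the irradiated region together with a fall from baseline that meets that cut-off. Define PR as meeting the cut-off with VAS above 0. The two are then exclusive and, at the 3-month visit, add up to the primary responders.
3. Report CR and PR on the same denominator as the primary endpoint. Removing low-baseline patients from the response tables alone would give percentages that cannot be compared with the primary one.
4. List patients whose baseline is too low for the required fall on a separate line, as remained pain-free or low baseline pain.
5. In the same edit, say whether CR is judged at each visit or requires VAS 0 at both.

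The cost is a sentence or two and one extra table line, using data already collected. The sample size does not change. The downside is a slightly less favourable CR rate.

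### Overall and bone survival start at diagnosis, before randomisation, which overstates survival and pulls the between-arm hazard ratio towards 1

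*Protocol article*

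**What the plan says.** Under Assessment of the primary and secondary endpoints, the protocol article states: "Overall survival is defined as time from initial diagnosis until death". In the same sentence, "bone survival is defined as time from initial diagnosis of spinal bone metastasis until death". Both belong to the secondary endpoints: "Secondary endpoints are QoL, fatigue, pain, overall survival, bone survival, local control, pathological fracture, and neurological deficit".

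Both starting points lie before allocation. The Inclusion criteria require a histologically confirmed tumour and diagnosed spinal metastases. Methods/design then says: "After the baseline results have been recorded, the patients will be randomly assigned to one of the two groups". Recruitment and randomization specifies 1:1 allocation, "stratified at baseline by pain level", and no stratification by time since diagnosis. It also says: "Regular study participation shall end 6 months after enrolment in the study or, where applicable, with the respective patient’s death".

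The article gives no other time origin for survival and does not mention delayed entry (left truncation).

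**The concern.** A patient can be randomised only if still alive. The time from diagnosis to randomisation is therefore free of deaths by design, and treatment cannot have influenced it. Including it in the survival time has two effects:

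- **Its length** adds to survival in both arms, so the curves and medians look better than survival after treatment, and the ratio of medians shrinks.
- **Its spread** between patients mixes the risk sets. At a given time since diagnosis, some patients counted as at risk have not yet entered the trial, and the rest are at very different times after treatment. This pulls the HR towards 1 and costs power.

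Most solid tumour types are eligible, so the interval may vary widely among 60 patients. The Discussion lists overall and bone survival among what this randomised study is to evaluate, so survival by arm is likely to be reported. From randomisation the two endpoints would be the same quantity; they differ only in pre-trial time.

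**Working it through.** **The plan's own figure.** The only numerical design statement is in Statistical analysis: "it will be possible to detect a standardized mean value effect of 0.74 with a power of" 80% at a 5% significance level, with 30 per group. A two-sided two-sample t-test gives a detectable effect of 0.736 at 80% power, and 80.5% power at 0.74. The figure reproduces. It does not concern survival.

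**Why the HR moves.** Suppose that at some time since diagnosis n1 and n0 patients (experimental, control) are truly under observation, and m more per arm are counted as at risk but not yet randomised. Deaths occur only among the former, in the ratio HR × n1/n0. The analysis divides by the wrong risk-set ratio:

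estimated HR = HR × (n1/n0) ÷ [(n1 + m)/(n0 + m)]

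With a true HR below 1, n1 tends to exceed n0, so adding equal m moves the estimate up. Made-up example: HR 0.5, n1 = 20, n0 = 10, m = 10 gives 0.5 × 2 ÷ (30/20) = 0.67. If every patient had the same interval, the order of deaths and the HR would be unchanged, so the spread causes this effect.

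**Inputs.** From the article: 30 per arm, 1:1 allocation, two-sided 5% (sidedness assumed), participation ending at 6 months. Assumed, because the article gives no survival data: exponential survival after randomisation, true HR 0.5, a log-normal pre-trial interval with the same distribution in both arms, and 24 months as a longer follow-up.

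**Simulation 1.** Control median 9 months, log-SD 0.8, log-rank test, 3000 trials per row.

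| Follow-up | Pre-trial median | HR: randomisation | HR: diagnosis | HR: delayed entry | Power: randomisation | Power: diagnosis | Power: delayed entry |
|---|---|---|---|---|---|---|---|
| 6 months | 6 months | 0.50 | 0.53 | 0.50 | 28.1% | 23.8% | 25.6% |
| 6 months | 12 months | 0.50 | 0.54 | 0.50 | 29.4% | 22.8% | 24.6% |
| 6 months | 36 months | 0.51 | 0.56 | 0.52 | 28.2% | 21.1% | 19.7% |
| 24 months | 6 months | 0.48 | 0.52 | 0.49 | 63.2% | 54.5% | 60.8% |
| 24 months | 12 months | 0.48 | 0.56 | 0.49 | 63.4% | 44.5% | 60.5% |
| 24 months | 36 months | 0.49 | 0.65 | 0.50 | 60.8% | 29.0% | 53.5% |

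Hand check of the randomisation column:

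- Expected deaths by 6 months are 30 × [(1 − 2^(−6/9)) + (1 − 2^(−6/18))] = 30 × (0.370 + 0.206) = 17.3, as simulated.
- Approximate power is Φ(√(17.3/4) × ln 2 − 1.96) = Φ(−0.52) = 30%.
- At 24 months, 43.4 deaths give Φ(0.32) = 63%.

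**Simulation 2.** Control median 8 months, pre-trial median 3 to 24 months, log-SD 0.8 to 1.

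- 6 months of follow-up: HR from diagnosis about 0.52 to 0.53; power from about 27-32% to 20-29%.
- 24 months of follow-up: HR about 0.51 to 0.64; power from about 62-65% to 26-62%.
- With 200,000 patients per arm, to remove sampling error, the same assumptions give HRs of 0.52 to 0.56 and 0.51 to 0.66. These wider ranges agree with simulation 1 and are the ones used here.

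**Medians (assumptions of simulation 1, no censoring).** From randomisation they are 9 and 18 months, a ratio of 2.0. From diagnosis, for pre-trial medians of 6, 12 and 36 months:

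- 17.4 and 26.7 months (ratio 1.53)
- 24.6 and 34.8 months (ratio 1.41)
- 50.0 and 62.6 months (ratio 1.25)

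**Type I error.** With a true HR of 1, rejection rates in simulation 1 were 4.4% to 6.2% from randomisation or diagnosis, and the highest value came from the randomisation origin. Simulation error is about √(0.05 × 0.95/3000) = 0.4 percentage points.

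**The case against.** The strongest reply is that little turns on these endpoints. Survival is secondary. The primary endpoint is pain at 3 months, and the sample size statement does not concern survival. Statistical analysis calls the tests descriptive and without confirmatory value. The Discussion's condition for larger trials names pain relief, local control and side effects, not survival. All of this stands and limits the severity. It does not remove the point, because a descriptive survival curve is exactly what this origin misstates. The origin is a stated definition, so the condensed format of an article does not explain it.

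A second reply is that at 6 months the distortion is small and power is low from either origin. That also stands: changing the origin does not make survival a well-powered comparison.

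Three stronger readings are tempting, and the documents do not support them:

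- **A reader might infer that the definition can create a false survival difference.** Time from diagnosis to randomisation is a baseline quantity with the same distribution in both arms under 1:1 randomisation. Chance imbalance in it is already covered by the test's error rate, which stayed near 5%.
- **A reader might infer that the comparison is nearly destroyed.** An HR of about 0.77 and a fall in power from 72% to 21% can be produced, but only with unlimited follow-up and an assumed 24-month median interval with log-SD 1. Neither is in the article.
- **A reader might infer that about 95% of the variance is pre-trial time.** In that scenario the interval has variance 24² × e × (e − 1) ≈ 2690, and uncensored control survival (8/ln 2)² ≈ 133, a share of 133/2823 = 4.7%. For both arms together, survival after randomisation has variance (133 + 533)/2 + 33 ≈ 366 (the 33 comes from the difference in arm means), a share of 366/3056 = 12%. Neither figure applies to censored data.

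**Conclusion.** The point holds as a fault of definition in two secondary endpoints. Both clocks start before randomisation, and a between-arm comparison on them without delayed entry overstates survival, attenuates the HR and loses power.

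For a true HR of 0.5, the estimate becomes about 0.52 to 0.56 at the 6-month end of regular participation. It becomes about 0.51 to 0.66 if deaths are followed to 24 months, where power falls from about 61-65% to 26-62%. The direction was the same in every scenario with a treatment effect. The size depends on assumed survival, effect and pre-trial interval, none of which the article gives.

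For bone survival the effect is probably smaller, because the interval since spinal metastasis is probably shorter. With an assumed 3-month median interval and 24 months of follow-up, the HR is only about 0.51.

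This should be fixed, but it is not critical: the primary endpoint, sample size and type I error are unaffected.

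**What to change.** For the between-arm comparison, define overall survival as time from randomisation to death from any cause, censored at last contact. Report time since tumour diagnosis and since diagnosis of spinal metastasis as baseline characteristics by arm.

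If survival from either diagnosis is kept, including bone survival, present it descriptively with delayed entry at randomisation, so that patients count as at risk only once enrolled. In simulation 1 this brought the HR back to 0.49-0.52 but did not always recover power, so it does not replace the randomisation origin for comparing arms.

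The cost is a change of definition, best made before survival is analysed. It needs no further patients, visits or measurements: it uses the dates of randomisation, death and last contact, plus the diagnosis dates that the present definitions already require.
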